#### Outcome measures

After screening, participants who satisfied the entry requirements will begin the run-in period. During this period, participants will document the four nasal symptoms on a diary card once per day. These scores for nasal obstruction, rhinorrhea, sneezing, and itching will be summed to yield the TNSS. Each symptom is graded on a five-point scale (0 = no symptom; 1 = mild; 2 = moderate; 3 = severe; 4 = very severe). Weekly averages of TNSS will be calculated and compared among groups throughout the study period. In addition, TNSS will be reviewed by an assessor blinded to the participants' treatment group at each visit. At the end of the run-in period, the RQLQ scores will be examined in the Korean and Mandarin Chinese versions of the questionnaire [20]. RQLQ measures the influence of AR on QoL and consists of 28 items in seven domains: sleep, non-hay fever symptoms, practical problems, nose symptoms, eye symptoms, activity, and emotional function in everyday life, all based on a sum score (range: 0 – 6). The RQLQ score will be blindly assessed three times: baseline, at the end of treatment, and at the end of the follow-up period. Participants in the active acupuncture group and sham acupuncture group will record their use of PER relief medications daily during the follow-up period.

We will estimate the expectation of participants using the credibility and expectancy questionnaire to determine whether expectations affected outcomes [21]. Blinding will be assessed by asking participants what arm they thought they were in (active or sham acupuncture group, or "don't know") at the end of trial, and why they believed they were in that arm. Adverse response of acupuncture will be recorded.

### Statistical methods

#### Analysis

Analysis will be performed for each of the following groups: 1) an intention-to-treat population consisting of all randomised participants with at least one measurable outcome report following acupuncture treatment (any missing data will be replaced with the last observation values); 2) a protocol-specific population including only participants without major protocol deviations. All data will be analysed descriptively. All main analyses will be based on the intention-to-treat population. For primary and secondary outcome measures, analysis of covariance (ANCOVA) using the differences in the change of outcome variable scores as the dependent variable, baseline outcome variable scores as the covariate, and allocated group and centres as the fixed factors will be performed. To compare the active acupuncture group with the sham acupuncture group and with the waitlist group, a single ANCOVA using dummy variables for the sham and waitlist group (thus coded 0, 0; 1, 0; 0, 1 for the active acupuncture group, sham acupuncture group, and waitlist group, respectively) will be conducted. All adverse events reported during the study will be included in the case report forms; the incidence of adverse events will be calculated. The percentage of subjects with adverse events in each group will be calculated and compared using the chi-squared test or Fisher's exact test.

Statistical analyses will be performed using the SAS statistical package program (ver. 9.1.3, SAS Institute Inc, Cary, NC), and the level of significance will be established at α = 0.05.

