**Methods:**

This study consists of a multi-centre (two centres in Korea and two centres in China), randomised, controlled trial with three parallel arms (active acupuncture, sham acupuncture, and waitlist group). The active acupuncture and sham acupuncture groups will receive real or sham acupuncture treatment, respectively, three times per week for a total of 12 sessions over four weeks. Post-treatment follow-up will be performed a month later to complement these 12 acupuncture sessions. Participants in the waitlist group will not receive real or sham acupuncture treatments during this period but will only be required to keep recording their symptoms in a daily diary. After four weeks, the same treatment given to the active acupuncture group will be provided to the waitlist group.

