### Primary outcome

Primary outcome will be the change in the weekly average of total nasal symptom score (TNSS) recorded in participants' diaries between the one-week of run-in period and the 4P^th ^week of the study. This scoring system was previously validated [14,16].

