#### Exclusion criteria

Participants will be excluded if they suffer from serious medical conditions, such as uncontrolled hypertension, diabetes mellitus requiring insulin injection, past or current malignant tumour, severe dyslipidaemia, liver or kidney dysfunction, anaemia, active pulmonary tuberculosis, or other infectious or systemic diseases inappropriate for treatment with acupuncture.

Participants will not be eligible if they have congenital nasal abnormalities, sinusitis, active asthma, a history of nose surgery, received systemically administered corticosteroids within six months prior to enrolment, or received alternative and complementary treatment, (i.e., acupuncture or herbal medication) for AR within the previous six months. Typical oral and nasal H1 blockers, intranasal/oral corticosteroids, or nasal anti-cholinergic medication will be stopped at least one week before enrolment. OTC drugs will be allowed for managing episodic colds, headaches, dyspepsia, etc. However, participants will be asked to disclose all medication use prior to enrolment. OTC drugs containing an H1 anti-histamine or anti-cholinergic component will not be allowed, since they may directly affect nasal symptoms. We will record the drugs taken by each participant at every visit, and participants will be requested to notify us of any change to their medication/supplement regimen. Additional acupuncture treatments, herbal prescriptions, or therapeutic intervention by other clinicians will not be allowed during the treatment period. Participants in the waitlist group will not receive acupuncture or sham acupuncture treatments during the study. After four weeks, if participants elect to try the acupuncture treatment, the real acupuncture treatment will be provided.

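### The main analysis set requires an outcome report after acupuncture, a condition the waitlist arm cannot meet by week 4, and it drops randomised participants who are never treated, so it is not intention-to-treat

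*Protocol article*

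**What the plan says.** Under Statistical methods, Analysis, the protocol article describes two populations. The first, called intention-to-treat, consists of "all randomised participants with at least one measurable outcome report following acupuncture treatment". Within it, "any missing data will be replaced with the last observation values". The section then states: "All main analyses will be based on the intention-to-treat population". It specifies "a single ANCOVA using dummy variables for the sham and waitlist group", with the active arm as reference, so the active versus waitlist contrast is estimated in the same model and on the same set as active versus sham.

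On the waitlist arm, the abstract says: "Participants in the waitlist group will not receive real or sham acupuncture treatments during this period". The Exclusion criteria section repeats this ("Participants in the waitlist group will not receive acupuncture or sham acupuncture treatments during the study") and adds: "After four weeks, if participants elect to try the acupuncture treatment, the real acupuncture treatment will be provided". During the four weeks the arm keeps a daily symptom diary.

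The primary outcome is the change in the weekly average nasal symptom score "recorded in participants' diaries between the one-week of run-in period and the" fourth week. Randomisation takes place at the end of the run-in (Design), by envelope at Visit 2 (Randomisation and allocation).

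**The concern.** Membership of the main set depends on two events after randomisation: having acupuncture, and then reporting an outcome. The first cannot happen in the waitlist arm before the primary endpoint, so the definition gives no usable rule for one of the three groups in the main model. Whoever builds the dataset must invent one, possibly after seeing data.

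In the two needled arms the first event can fail to happen. Someone randomised who never attends a session is left out, diary or no diary. Keeping every randomised person in the comparison is the purpose of an intention-to-treat analysis, and this rule gives it up while using the name. If the analyst keeps waitlist participants on the strength of their diaries but still requires treatment in the active arm, the two sides of active versus waitlist are selected by different rules.

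**Working it through.** This is a question of definition, so the main check is to apply the stated rule to each arm, using data up to week 4.

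| Arm | Planned | Acupuncture by week 4 | Diary by week 4 | In the set as written |
|---|---|---|---|---|
| Active | 95 | Real, 12 sessions | Yes | Only if treated and a later report exists |
| Sham | 95 | Sham, 12 sessions | Yes | The same, provided sham counts as acupuncture treatment |
| Waitlist | 48 | None | Yes | Nobody: 0 of 48 |

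Four things follow.

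1. **Waitlist.** A report after acupuncture can exist only after week 4, later than the primary endpoint. Taken at its word, the rule excludes 48 of 238 = 20% of the planned sample.
2. **Needled arms.** Randomisation comes before any session. A person who is randomised, keeps the diary and is never needled has outcome data but fails the condition.
3. **Data are not the obstacle.** The Inclusion criteria require a completed baseline diary, so each randomised participant should have a baseline. The post-randomisation diary does not depend on being treated.
4. **Timing is loose.** The condition could mean after the first session or after the full course. Carrying forward last values suggests the first, but the text does not say.

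**Is power affected?** First, the protocol's own sample size (inputs from the Sample size section):

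- Adjusted SD = 4.74 × 1.148 = 5.44.
- Difference 2.53, alpha 0.025 two-sided, power 80%, normal approximation: 88 per group.
- ANCOVA factor 1 − 0.76² = 0.4224; 88 × 0.4224 = 37.2, rounded up to 38. This matches the stated 38.
- With 2:2:1 allocation and 20% withdrawal: 76/0.8 = 95 and 38/0.8 = 47.5, rounded up to 48. Total 95 + 95 + 48 = 238, as stated.

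Then power under exclusions. The residual SD is 5.44 × √0.4224 = 3.54. Power comes from the noncentral t distribution with noncentrality 2.53/(3.54 × √(1/n₁ + 1/n₂)) and alpha 0.025 two-sided. The protocol gives no rate of untreated participants, so the exclusion rates below are assumptions. The last column keeps all 48 waitlist participants and uses the same difference of 2.53, although the protocol expects a larger one against waitlist.

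| Assumed share of each needled arm excluded | n per needled arm | Power, active v sham | Power, active v waitlist (48) |
|---|---|---|---|
| 0% | 95 | 99.6% | 96.1% |
| 5% | 90 | 99.4% | 95.8% |
| 10% | 86 | 99.2% | 95.5% |
| 20% | 76 | 98.3% | 94.5% |

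Loss of power is not the problem. What remains is an undefined comparator set and selection after randomisation.

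**The case against.** The strongest reply is that the authors meant at least one post-baseline report. Much supports this: the waitlist arm is coded into the ANCOVA, sized in the Sample size section, asked to keep a diary, and included in the comparison of weekly averages among groups. A reader might infer from the wording that all 48 waitlist participants will be dropped, or that the contrast will rest on those who later choose acupuncture. The documents do not support either as an expected result: they plainly intend to analyse the arm, and the elective treatment comes after the week-4 endpoint. This stands as an account of intention. It does not repair the rule, which says something else. Even on the generous reading the set still excludes randomised participants with no later report, which makes it a modified set under an intention-to-treat label.

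A second reply concerns active versus sham. A reader might infer that early leavers bias this contrast. Under Randomisation and allocation, these participants are not told which treatment they receive until the end of the study, and practitioners may not discuss treatment with them. Someone who leaves before a first session has experienced neither procedure, so the reason for leaving can hardly depend on which was assigned. After the first session the diary is daily, so the gap to a first report is short. This reply largely stands. It does not extend to active versus waitlist, where participants know whether they have been put on the waiting list.

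Third, the 20% withdrawal allowance should not be read as the share excluded by this rule. It covers all withdrawal, and anyone who reports once after treatment and then withdraws stays in the set.

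**Conclusion.** The point holds as a defect in the stated rule, not as missing detail. The set that governs every main analysis is defined by a condition one of its three arms cannot meet by the primary endpoint, and it excludes randomised participants who were never treated. It is not an intention-to-treat set.

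Its size in bias terms cannot be calculated, because the protocol gives no rate of randomised but untreated participants and nothing on how their outcomes would differ. The selection risk is mainly in active versus waitlist and small in active versus sham; the latter judgement assumes that blinding between the needled arms works as described. Power is adequate throughout the assumed range of 0% to 20% exclusions, and the sample size needs no change.

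**What to change.** Define the main analysis set as all randomised participants, analysed in the arm assigned, whether or not any treatment was received, and count outcomes from randomisation in all three arms.

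If the investigators still want at least one post-randomisation diary report as a condition, they should:

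- apply it in identical terms to all three arms, with no reference to treatment;
- call the set modified intention-to-treat;
- add a sensitivity analysis that includes participants with no post-randomisation report, stating what is assumed about their outcomes.

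The cost is a change of wording and a little more analysis work for participants without follow-up diaries. Sample size and data collection stay as they are. Whether to keep carrying forward the last value or use another missing-data method is a separate point and need not be settled to correct the definition.

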#### Sample size

For power analysis and sample size calculation, we conducted a pilot study with a sample size of 19 (9 in the active acupuncture arm and 10 in the sham acupuncture group). In this study, the pooled SD of TNSS was 4.74 and the mean difference of TNSS change between the active and sham acupuncture group was 2.53. This difference was larger than that of recent successful acupuncture RCT on PER, reported as 1.8 [14]. TNSS reduction in the active acupuncture group in our pilot study was 4.12, higher than the minimal clinically important differences (i.e. 2.2) [22]. Therefore, the result of our pilot study showed the potential of acupuncture treatment and supported the need for the present trial. The SD of the pilot study was adjusted for better application to the true population. In order to achieve this adjustment, we multiplied the SD from the pilot data by a correction factor of 1.148. This adjustment provides a 75% probability that the resulting estimate of SD will be at least as large as the true population SD [23]. For the sample size calculation, we established a sample size (N) for an independent t test using the adjusted SD, and the difference in TNSS change between the active and sham acupuncture group with a power of 80% and alpha value of 2.5% (two-tailed). We then estimated a Pearson correlation value (R) of 0.76 between baseline and the change of TNSS in our pilot study. Finally, we multiplied N by (1-R^2^) to yield the sample size needed for ANCOVA analysis [24]. The results indicated that the number of subjects in the active acupuncture group and in the sham acupuncture group was 38. If we compare the change in TNSS for the active acupuncture group with that of the waitlist group, assuming that pooled SD and R are similar to our pilot study, the differences between groups will be larger, and thus 38 subjects in the waitlist group size will be enough to detect significant differences in the change in TNSS for the active acupuncture group. We applied a 2:2:1 ratio to the active acupuncture group, sham acupuncture group, and waitlist group, respectively, and we expect that this allocation ratio will raise the statistical power. We plan to enrol 95, 95, and 48 participants in the active acupuncture group, sham acupuncture group, and waitlisted group, respectively, allowing for a 20% withdrawal rate.

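### Carrying the last score forward in the main analysis misstates week 4, in a direction that depends on who leaves; a likelihood model on the planned weekly scores is better

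*Protocol article*

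**What the plan says.** The Primary outcome section defines the endpoint: "Primary outcome will be the change in the weekly average of total nasal symptom score (TNSS) recorded in participants' diaries", taken from the run-in week to week 4. The Analysis section describes the intention-to-treat population and adds in parentheses that "any missing data will be replaced with the last observation values". It continues: "All main analyses will be based on the intention-to-treat population". The model is an ANCOVA on change with "baseline outcome variable scores as the covariate, and allocated group and centres as the fixed factors will be performed". The one other analysis set leaves out major protocol deviators. It is not a missing-data sensitivity analysis.

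The Sample size section sets enrolment at 95, 95 and 48, "allowing for a 20% withdrawal rate". It does not say over what period the 20% is counted.

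Under Outcome measures, TNSS comes from a daily diary and "Weekly averages of TNSS will be calculated and compared among groups throughout the study period". The quality-of-life score is sparser: "The RQLQ score will be blindly assessed three times", namely at baseline, end of treatment and end of follow-up.

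**The concern.** LOCF treats a participant who leaves after week 1 or 2 as if the score then reached had been observed in week 4. That is harmless only if scores stand still, and the protocol expects them to move. In its pilot the active arm fell by 4.12 and the difference from sham was 2.53, which implies a sham fall of 4.12 − 2.53 = 1.59.

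The error in an arm grows with that arm's expected improvement and with the share who leave. It need not cancel between arms. Depending on the pattern, LOCF can shrink a real difference, leave it almost unchanged, or produce one where none exists.

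Withdrawal related to symptoms is plausible, because relief medication is stopped throughout run-in and treatment. Unequal withdrawal is most plausible for the waitlist, which is untreated and knows it, and active versus waitlist is a planned contrast. The rule sits in the main analysis, so the headline estimate is at stake. The weekly scores needed for a better method are already planned.

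**Working it through.** **The plan's own figure.** Inputs from the Sample size section: "the pooled SD of TNSS was 4.74 and the mean difference of TNSS change between the active and sham acupuncture group was 2.53"; correction factor 1.148; R = 0.76; power 80%; two-sided alpha 2.5%.
- Adjusted SD = 4.74 × 1.148 = 5.44.
- n per group = 2 × (2.241 + 0.842)² × (5.44/2.53)² = 88 (normal), or 90 with the exact t distribution.
- Multiplied by 1 − 0.76² = 0.4224: 37.2 or 38.0. The stated 38 reproduces.
- Withdrawal: 38/0.8 = 47.5, so 48; 76/0.8 = 95. These also reproduce.

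**Assumptions not in the documents.** Improvement is linear over weeks 1 to 4, exits are spread evenly after weeks 1, 2 and 3, and the split of withdrawal by arm is as shown.

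**Bias by hand.** A leaver carries forward on average (0.25 + 0.50 + 0.75)/3 = 0.5 of the full change. With a proportion d leaving, the mean LOCF change in an arm is change × (1 − d/2).

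| Leaving, active/sham | Arithmetic | LOCF difference | Simulated LOCF | Simulated likelihood model |
|---|---|---|---|---|
| 20%/20% | 4.12 × 0.90 − 1.59 × 0.90 | 2.28 | 2.30 | 2.56 |
| 30%/10% | 4.12 × 0.85 − 1.59 × 0.95 | 1.99 | 1.97 | 2.54 |
| 10%/30% | 4.12 × 0.95 − 1.59 × 0.85 | 2.56 | 2.55 | 2.52 |

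The true value is 2.53 throughout. The simulation used 1,500 trials per row with 95 v 95, residual SD 3.54 and weekly correlation 0.7 (assumed). When leaving depended on the last observed score, 20%/20% gave LOCF 2.29 and the likelihood model 2.53.

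**No true difference.** If both arms improve by 4.12, the false difference is 4.12 × (0.95 − 0.85) = 0.41 at 10%/30%, and 4.12 × (0.925 − 0.875) = 0.21 at 15%/25%. At equal withdrawal it is zero.

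**Type I error.** This also needs a residual SD. The protocol's figures give 4.74 × √0.4224 = 3.08, or 3.54 after the correction factor. With λ = false difference / (SD × √(2/95)), the two-sided rejection rate at nominal 5% is approximately Φ(−1.96 + λ) + Φ(−1.96 − λ). For SD 3.54 the standard error is 0.514.

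| Scenario, 95 v 95 | False difference | λ | Approximate | Simulated |
|---|---|---|---|---|
| 20%/20%, improving 4.12 | 0 | 0 | 5.0% | 4.5% |
| 15%/25%, SD 3.54 | 0.21 | 0.40 | 6.9% | 6.6–7.1% |
| 10%/30%, SD 3.54 | 0.41 | 0.80 | 12.6% | 11.4–12.6% |
| 10%/30%, SD 3.08 | 0.41 | 0.92 | 15.2% | 15.0% |
| 10%/30%, both improving only 1.59, SD 3.54 | 0.16 | 0.31 | 6.1% | 5.4% |

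Other simulated values:
- With weekly SD 3.5 and within-person correlation 0.6 (residual SD 3.5 × √(1 − 0.6²) = 2.8), 10%/30% gave 15.8% and 16.7% in separate runs, and 15%/25% gave 8.3%.
- With an early response (60, 85, 95 and 100% of the change by weeks 1 to 4) and that same smaller SD, 10%/30% gave 6.8% (false difference 4.12 × 0.20 × 0.20 = 0.16). Early response at 15%/25% gave 5.3%.
- At 95 v 48, the size of the waitlist contrast, with 10%/30%, LOCF gave 9.4% and the likelihood model 4.5%.

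Across the no-difference scenarios in which it was fitted, the likelihood model stayed at about 4–5%.

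**The case against.** The strongest reply is that the harm depends on inputs the protocol does not give, and much of that stands.

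- A reader might infer that LOCF inflates type I error whatever happens. It does not: with equal withdrawal the rate stays near 5% and only the estimate shrinks.
- A reader might expect a large imbalance between active and sham. Nothing in the article predicts one. Those participants are blinded, attend the same visits and face the same medication bar. The waitlist is the likelier source, but the 9.4% for 95 v 48 still supposes that an untreated arm improves by 4.12, which is hard to assume.
- The upper type I figures need linear improvement, a full 4.12 in both arms and a small residual SD together. An early response or a smaller improvement brings 10%/30% close to nominal.
- The 20% may cover all nine weeks, so fewer may be missing at week 4. At 5%/15%, otherwise under the assumptions that gave the highest rates, type I error was 7.6%.
- It is tempting to add that filled-in values give wrong standard errors. No figure here supports a material effect, and the near-nominal rate under equal withdrawal argues against one.
- The likelihood model is valid only if data are missing at random, and the weekly-score argument does not reach RQLQ.

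What survives is that LOCF is fixed for the main analysis, its assumption conflicts with the improvement the protocol expects, and a better method needs no new data.

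**Conclusion.** The point holds in conditional form. LOCF in the main analysis misstates week-4 TNSS for leavers, and the sign and size of the resulting error depend on the withdrawal pattern. Under linear improvement with exits over weeks 1 to 3, a true 2.53 is estimated at about 2.3 (20%/20%), about 2.0 (30% active/10% sham) or about 2.55 (10% active/30% sham). Type I error is near 5% with equal withdrawal, about 5–8% at 15%/25%, and about 6–16% at 10%/30% (single runs 5.4% to 16.7%). These are illustrations, not forecasts, because the article gives neither a trajectory nor a split by arm. They do show that LOCF cannot be defended as conservative.

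One might also infer that the trial is too small. It is not: at the assumed effect, power with 95 per arm stayed at about 95% or more in the simulations, even under LOCF. The issue is the validity of the estimate and, if withdrawal is unequal, of the test.

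**What to change.** Make the primary TNSS analysis a likelihood-based repeated-measures model (MMRM) on the weekly averages for treatment weeks 1 to 4. Include arm, week, arm-by-week, baseline, baseline-by-week and centre. Take the week-4 contrasts of active with sham and with waitlist as primary, and state that the model assumes missing at random.

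Add one delta-adjusted analysis for data not missing at random, and keep LOCF only as a sensitivity analysis.

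For RQLQ, use multiple imputation, for example with weekly TNSS among the predictors. It has a single end-of-treatment value, so for someone who leaves during treatment LOCF can only carry baseline forward and record zero change.

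The cost is wording in the protocol and analysis plan and a little programming, to be settled before unblinding. No new data or visits are needed, and enrolment of 95, 95 and 48 stays as it is.

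### The single three-arm ANCOVA pools variance and slope with an unpiloted waitlist arm, so ordinary standard errors can be off: materially for active v waitlist, modestly for active v sham

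*Protocol article*

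**What the plan says.** The Analysis section applies the same ANCOVA to primary and secondary outcomes. The change score is the response, with "baseline outcome variable scores as the covariate, and allocated group and centres as the fixed factors will be performed". Both comparisons of the active arm come from "a single ANCOVA using dummy variables for the sham and waitlist group", and the dummy coding is written out. The section mentions no baseline-by-group term, arm-specific variance or robust standard error.

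The Sample size section rests on a pilot with "9 in the active acupuncture arm and 10 in the sham acupuncture group" and no waitlist. For the waitlist arm it proceeds by "assuming that pooled SD and R are similar to our pilot study". Allocation is 2:2:1, with 95, 95 and 48 enrolled and 20% withdrawal allowed for.

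**The concern.** On its ordinary reading, an ANCOVA of this form estimates one residual variance and one baseline slope for all three arms. The needled arms and the waitlist differ in ways that could affect both. Waitlist participants receive no needling for four weeks and know it. The pilot correlation of 0.76 between baseline and change comes from needled participants only, and it may include treatment response that scales with baseline.

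If the waitlist's residual spread differs, the pooled variance is wrong for each contrast, and in opposite directions. A more variable waitlist makes active v waitlist too liberal and active v sham too conservative. A less variable waitlist does the reverse. The sham comparison needs no waitlist data, yet its standard error moves with the waitlist's spread. At stake are the false-positive rate and interval coverage, not the estimates themselves.

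**Working it through.** **1. The plan's own figure.** Inputs from the Sample size section: SD 4.74, correction factor 1.148, difference 2.53, R = 0.76, 80% power, two-sided alpha 2.5%.
- Adjusted SD: 4.74 × 1.148 = 5.44.
- The two-group normal formula gives 88 per group, and 88 × (1 − 0.76²) = 88 × 0.4224 = 37.2, rounded up to 38. The exact t test gives 90, and 90 × 0.4224 = 38.02. The stated 38 reproduces.
- Residual SD implied by the plan: 5.44 × √0.4224 = 3.54.
- Completers after 20% withdrawal: 95 × 0.8 = 76, and 48 × 0.8 = 38.4, so 76/76/38 with N = 190.

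**2. Closed form.** Let r be the waitlist residual SD divided by that of the needled arms. The document does not give r, so 0.7 to 1.5 is an assumed range. In units of the needled arms' residual variance:
- Pooled variance: P = [(76−1) + (76−1) + (38−1)r²] / (190−3).
- Model SE / true SE, active v sham: √P.
- Model SE / true SE, active v waitlist: √{P(1/76 + 1/38) / (1/76 + r²/38)}.
- True two-sided error at nominal 5%: 2Φ(−1.96 × ratio).

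Worked for r = 1.5: P = (75 + 75 + 37 × 2.25)/187 = 233.25/187 = 1.247. Active v sham: √1.247 = 1.117, true error 2.9%. Active v waitlist: √(1.247 × 0.03947 / 0.07237) = √0.680 = 0.825, true error 10.6%.

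| r (assumed) | P | SE ratio, active v sham | True error | SE ratio, active v waitlist | True error |
|---|---|---|---|---|---|
| 0.7 | 0.899 | 0.948 | 6.3% | 1.167 | 2.2% |
| 1.0 | 1.000 | 1.000 | 5.0% | 1.000 | 5.0% |
| 1.25 | 1.111 | 1.054 | 3.9% | 0.899 | 7.8% |
| 1.5 | 1.247 | 1.117 | 2.9% | 0.825 | 10.6% |

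The pattern is the same at the 2.5% level used for sample size: r = 1.5 gives 1.2% and 6.5%.

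**3. Simulation.** 6,000 trials per case at 76/76/38, residual SD 3.54, assumed baseline SD 4.14, with baseline and centre in the model:

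| Waitlist scenario (assumed) | Active v sham | Active v waitlist |
|---|---|---|
| SD ratio 0.7 | 6.2% | 2.2% |
| SD ratio 1.25 | 4.0% | 7.7% |
| SD ratio 1.5 | 2.9% | 10.5% |
| SD ratio 1.5, slope −0.4 v −1.0 in the other arms | 2.8% | 11.5% |
| Equal SD, slope zero | 3.5% | 8.5% |

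With HC3 standard errors, both contrasts lay between 4.1% and 5.2% in every case.

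**4. The role of 2:2:1.** Compare with equal arms at the same N.
- r = 1.5: P ≈ (2 + 2.25)/3 = 1.417. The active v sham ratio is √1.417 = 1.19 (true error 2.0%), against 1.117 at 2:2:1. The active v waitlist ratio is √(1.417 × 2/3.25) = 0.934 (6.7%), against 0.825 (10.6%).
- r = 0.7: P ≈ (2 + 0.49)/3 = 0.83. The active v sham ratio is 0.911 (7.4%), against 0.948 (6.3%).

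The half-size waitlist therefore aggravates the error for active v waitlist and slightly reduces it for active v sham.

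**The case against.** The strongest reply is that the article fixes the mean model and names no variance estimator. Equal-variance ANCOVA is conventional, and an analysis plan that is not shown could add robust errors without contradicting the text. This stands to the extent that the plan contains no contradiction here. It does not dispose of the point. The stated model, run as usual, has the behaviour shown above, and the remedy is a definite method rather than a request for detail.

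Second, a reader might infer that the plan rests its analysis model on the assumed similarity of waitlist and pilot. The text does not support that: the assumption is made openly, and only to size the waitlist arm.

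Third, a reader might infer that 2:2:1 allocation damages both contrasts. Step 4 of the working shows that it does not.

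Fourth, unequal spread is not established. All arms share the eligibility criteria, the same bounded 0 to 16 diary score and the instruction to stop relief medication. An untreated arm, lacking variation in treatment response, could well be less variable, and active v waitlist would then be conservative. This stands: the document settles neither the size nor the direction. Doubling the error rate needs r near 1.5, a residual variance 2.25 times that of the needled arms. At r of 0.9 to 1.1 the true error is only 4.5 to 5.5% for active v sham and 4.0 to 6.1% for active v waitlist.

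**Conclusion.** The point holds as a conditional weakness with a cheap remedy. If the waitlist's residual spread or slope differs from that of the needled arms, ordinary ANCOVA standard errors are wrong. Over assumed SD ratios of 0.7 to 1.5, the true error at nominal 5% runs from about 2% to about 10% for active v waitlist, and to about 12% at ratio 1.5 with the assumed slope difference. For active v sham it runs from about 6% down to about 3%, so the interval is between about 5% too narrow and 12% too wide.

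These figures rest on ratios, slopes and a baseline SD that the document does not give. They do not show that the error bars will be wrong. Nor do they cast doubt on the point estimates, which randomisation keeps unbiased under this model, or on the stated sample size, which reproduces. A reader might infer that the sham comparison is seriously compromised, but the calculation shows only a modest effect there.

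**What to change.** Keep the single ANCOVA for the point estimates. Before unblinding, prespecify that tests and confidence intervals for the primary and the continuous secondary outcomes use either arm-specific residual variances (mixed-model procedure) or heteroscedasticity-consistent HC3 standard errors. Name one of the two, so that the choice cannot depend on the data.

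The cost is one sentence and one program option. The sample size does not change. If the variances are in fact equal, the loss of efficiency is negligible, and the simulated HC3 error rates stayed close to nominal.
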